#### Lipoaspiration procedure

For patients receiving the adipose tissue injection, fat tissue will be harvested under semi-sterile conditions (sterile draping and gloves, gown, face masks, and head cover). The participant will be positioned supine on an examination bench. Local anesthesia (2% lidocaine) will be applied to the area to be harvested (approx. 8 cm × 20 cm just below the umbilicus) and a small incision (6-8 mm) will be made. Approximately 500 mL of normal saline containing 50 mL of 2% lidocaine and 1amp epinephrine will be infused to reduce bleeding and trauma. Approximately 15 min will be allowed for infiltration. Then, a thin cannula will be inserted through the incision and a controlled back and forth motion will be used to loosen excess fat. Using a 13-gauge cannula connected to a VacLok® syringe, 20 ml to 40 ml of subcutaneous adipose tissue will be harvested. Following the harvest procedure, a pressure dressing will be applied. Participants will be told to remove the dressing 24–48 h after the procedure and return approximately 1 week after receiving the treatment so that the harvest site can be evaluated.

We will assess participants using a proprietary system that includes a force plate (1000 Hz (9260AA6, Kistler Instruments, Winterthur, Switzerland), dedicated computer, and software (SpartaMARS, Sparta Performance Science, Menlo Park, USA). Participants will be assessed at baseline, 6 weeks and 6 months. The non-invasive standing assessment will take approximately 3 min to complete. Assessments will be performed after clinical outcome data has been obtained, but before synovial fluid has been aspirated. Participants will be instructed to stand on the scale with their hands on their hips and eyes closed to establish baseline force. The test consists of four, 20 s balance trials on each leg. A 10 s rest period will be provided between trials, and trials will be conducted on alternating legs. Displacement and sway velocity will be measured as described previously [62]. The results of the force plate assessment will be associated with clinical outcome data and synovial fluid biomarker profiles. Results of the force plate sub-set analysis will be reported separately.

Excess adipose tissue will be transferred to sterilized vials filled with phosphate buffered saline. Adipose tissue samples will be kept at 4 °C. Samples will be divided into two parts in the biosafety hood using sterile scalpel. One part of each sample will be processed for cell culture, and another part will be cryopreserved. For cell culture, samples will be transferred to a tube containing RPMI serum free medium, supplemented with 1% penicillin-streptomycin-fungizone. Tissue samples will be washed 3 times with the same medium, then finely minced for cell isolation using a standard collagenase digestion protocol.

Synovial fluid samples will be transferred to EDTA tubes, gently inverted 8–10 times, and then immediately transported to the lab on wet ice in accordance with university policies. Samples will be centrifuged within 1 h at 1500 x g for 10 min at 4 °C. The supernatant will then be aliquoted to cryovials containing protease inhibitor and stored at -80C until use.

Synovial fluid samples and excess adipose tissue will be analyzed to characterize the treatment and gain a better understanding of how adipose tissue affects the biochemical environment of the knee. To better monitor the disease progression and treatment efficacy, chemokines, cytokines, growth factors, and matrix metalloproteinases in the synovial fluid will be analyzed, including IL-1β, IL-6, IL-8, TNFα, C-terminal telopeptides of Type I collagen, and C-telopeptide of Type II collagen. The results will be made available for principle component analysis, which will be used to determine if pre-treatment synovial fluid inflammatory mediator and selected OA biomarker profiles that define different OA phenotypes predict the responses to autologous adipose tissue injections. The pro- and anti-inflammatory capabilities and cell viability of the autologous fat product will be evaluated and may also be compared to unprocessed preparations.

The use of NSAIDs may negatively impact healing [32, 63] and their prolonged half-life in synovial fluid allows them to accumulate in the joint [64], which is likely to impact synovial fluid biomarker profiles. To ensure that clinical outcomes, tissue healing and the biochemical profile of the synovial fluid are not influenced by the use of NSAIDs, participants will be asked not to take NSAIDs for at least 1 week prior to treatment and throughout the duration of the study.

Patients will be instructed to contact the study doctor before taking analgesic medications. Acetaminophen (250-500 mg) will be recommended if appropriate. The total number of days each patient takes acetaminophen will be logged and reported with published results. However, extended acetaminophen used will not be used as grounds for termination, as it has it is generally thought to have a clinically negligible effect on OA-related knee pain [65–67].

### Assignment of interventions

A random number sequence was generated using the Stata 14.0 uniform distribution. Blocks of four were used to ensure equal numbers of subjects in each group. To carry out the randomization of study subjects, we will utilize sequentially numbered, opaque, sealed envelopes. The statistician will prepare the envelopes for the Principal Investigator in order to maintain the concealment of the sequence prior to randomization. Upon enrolment in the trial, the next sequentially numbered envelope will be selected by the investigator and the subject will be offered the assigned treatment.

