**Methods:**

This is a prospective, single-center, parallel-group, randomized, controlled trial. Participants (*n* = 54) will receive either a single intra-articular, ultrasound-guided injection of autologous adipose tissue or a single intra-articular, ultrasound-guided injection of HA (1:1 ratio). Outcome data will be obtained at baseline, week-6 and month-6. The Western Ontario and McMaster Universities Osteoarthritis Index (WOMAC) pain domain (WOMAC-A) will be used as the primary outcome measure. Secondary clinical outcome measures include WOMAC (full), clinical anchors (pain, function, and stiffness), and the 29-point Patient-Reported Outcomes Measurement Information System (PROMIS®) profile. We will also take synovial fluid samples and assess sway velocity using a force plate, as well as analyze excess/discard adipose tissue to gain a better understanding of how intra-articular adipose tissue injections influence the biochemical environment of the joint.

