### Study overview

This is a prospective, single-center, parallel-group, randomized, controlled study. The aim of this study is to estimate statistical power and gather preliminary efficacy data. Qualified participants will receive either a single, intra-articular injection of autologous adipose tissue or a single, intra-articular injection of HA. We hypothesize that participants treated with autologous adipose tissue will show a greater improvement in pain (as determined using the pain items of the Western Ontario and McMaster Universities Osteoarthritis Index, or WOMAC-A) than participants treated with HA. WOMAC (full questionnaire), the 29-point Patient-Reported Outcomes Measurement Information System (PROMIS®) profile, and clinical anchors will be used as secondary clinical outcome measures. Synovial fluid samples and excess adipose tissue (treatment group) will also be analyzed to gain a better understanding of how adipose tissue affects the biochemical environment of the joint.

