## Methods

### Participants, interventions, and outcomes

All study-related activities will be performed at the USC Department of Orthopaedic Surgery Outpatient Clinic, including subject identification, screening, treatment, and outcome assessments. Patients between the ages of 45 and 75 with Kellgren-Lawrence grades 2–3 OA (inclusive) that are interested in participating in the study will be screened for eligibility by the principal investigator using pre-defined criteria (Fig. 1). Those who meet inclusion/exclusion criteria and decide to participate will sign an informed consent before randomization (see Assignment of Interventions). Because the fat treatment requires the removal of adipose tissue from the abdomen, participants will not be blinded to their assigned group.

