**Fig. 1 Fig1:**
[figure not shown]
Study design flow chart

Male and/or female patients will be randomized to either the HA (Synvic One®) treatment group (*n* = 27) or autologous fat (Lipogems®) treatment group (n = 27). To ensure enrollment goals are met, the investigator will draw from a waitlist of current patients that have expressed interest in participating in clinical trials. We also have IRB-approved flyers/brochures that will be shared with patients and nearby orthopaedic clinics (Additional file 1). Additionally, to improve adherence to the intervention protocol, participant who are allocated to the control group that complete all scheduled follow-up visits will be offered the adipose tissue treatment at the end of their final visit at no cost.

Since our primary aim is to estimate the effect size for future well-powered studies, we estimate the precision around which we can measure the effect. Based on a prior study using similar methods, but comparing WOMAC-A scores among patients receiving placebo to Hylan G-F (a joint lubricant) [54], we assumed standard deviations in the control and treatment groups of 0.66 and 0.67, respectively. With a sample size of 54 (27 per group), we will be able to estimate a two-sided 95% confidence interval within ±0.36 distance from the mean difference. For our secondary aim, we estimated the mean difference we would be able to detect, assuming a similar effect size for HA as was observed for Hylan G-F (μ = − 0.84, σ = 0.67) and found that we would have 80% power to detect a mean difference of − 1.4 in the autologous adipose group with a two-sided Type I error rate of 0.05.

Power was calculated using Pass 14 (Kaysville, UT).

At the treatment visit (day 0), patients will be randomly assigned to receive either a single intra-articular, ultrasound-guided injection autologous adipose tissue (6 ml) or a single intra-articular, ultrasound-guided injection of hyaluronic acid (6 ml). Patients with bilateral OA will be allowed to participate in this study, but only their more painful eligible knee will be treated (as determined by WOMAC-A). To control for possible responder differences between bilateral and unilateral symptomatic patients [55, 56], WOMAC-A for the contralateral knee will be obtained at baseline, 6 weeks, and 6 months (Table 1). If a participant has bilateral OA of equal pain intensity in both knees, the treatment knee will be selected randomly.

**Table 1 Tab1:** Study Calendar

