### Ethics and dissemination of information

Ethics approval was received from the University of Southern California Health Science IRB (10/9/2017), USC Institutional Biosafety Committee (May 2017) and USC Radiation Safety Committee (September 2017). Continuing reviews and all protocol modifications will be submitted to the USC Health Science IRB through the University iStar System. Because the IRB has determined that this study involves ‘greater than minimal risk’, only the Principal Investigator will be allowed to obtain informed consent. All participants provided written informed consent to participate. Participants will be given a copy of the consent to take home, and an informed consent comprehension assessment will be performed before randomization.

To protect participant confidentiality, samples will not be labeled with information that can be used to directly identify participants. Samples will be labeled with subject identification numbers and only the investigator and IRB-approved study personnel will have access to information linking subject identification numbers to identifiable information. The link between study participants and their study ID numbers will be destroyed (shredded/purged) in accordance with federal regulations when study activities are complete. The final trial dataset will not contain identifiable data and will be available to all investigators listed in the IRB protocol.

There are no additional provisions for ancillary or post-trial care, or for compensation to those who suffer harm from trial participation. However, participants will be informed prior to enrollment that they are responsible for unscheduled visits/interventions and that they are not giving up any legal rights by agreeing to participate in the study (Additional file 4). Once study activities have been completed, results will be published and posted to clinicaltrials.gov.

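### Fixed blocks of four, in an open single-centre trial where the principal investigator screens, consents and takes the next envelope, make about one third of allocations deducible

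*Protocol article*

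**What the plan says.** Under Assignment of interventions, the protocol article says: "Blocks of four were used to ensure equal numbers of subjects in each group". It gives no second block size and no strata. The envelopes are numbered in sequence, opaque and sealed, and the statistician prepares them. At enrolment "the next sequentially numbered envelope will be selected by the investigator and the subject will be offered the assigned treatment".

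Other sections give the setting:
- **Design** (Study overview): "This is a prospective, single-center, parallel-group, randomized, controlled study". The Abstract gives the 1:1 ratio.
- **Blinding** (Participants, interventions, and outcomes): "participants will not be blinded to their assigned group".
- **Screening** (same section): done by the principal investigator against pre-defined criteria.
- **Recruitment** (same section, after Fig. 1): "the investigator will draw from a waitlist of current patients that have expressed interest in participating in clinical trials". Flyers and nearby clinics are a further source.
- **Consent** (Ethics and dissemination of information): "only the Principal Investigator will be allowed to obtain informed consent".
- **Timing** (Table 1): screening and consent fall between day −21 and day 0, and allocation falls on day 0.

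**The concern.** Concealment has two parts: nobody can read the next assignment, and nobody can infer it. The envelopes deal with the first. The second fails when block size is constant and known, past assignments are visible, and the person who sees them also influences who comes next. The article prints the block size and does not say that it is withheld from the investigator. Treatment is open, and the investigator handles each envelope.

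What is at stake is the comparability of the groups at entry. The Discussion acknowledges investigator bias and offers self-reported outcomes, direct data entry and blinded laboratory analysis. These protect measurement, not enrolment. The Discussion also counts protection from selection bias among the strengths of a randomized trial, and that protection depends on unpredictable assignment. The primary aim is an effect size for planning later studies, so any selection effect would carry over into those plans.

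**Working it through.** **Inputs.** Block size 4 (Assignment of interventions); ratio 1:1 (Abstract); one centre and no stated strata, hence one running sequence (Study overview); N = 54, 27 per group, with SDs 0.66 and 0.67 (sample-size paragraph in Participants, interventions, and outcomes).

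**The plan's own figure.** The article gives no predictability figure. Its stated precision reproduces: standard error = √(0.66²/27 + 0.67²/27) = 0.181. The half-width is 0.363 with the t quantile on 52 degrees of freedom and 0.355 with the normal quantile, against the stated ±0.36. The point here does not depend on it.

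**Certain allocations.** A 2+2 block has 6 equally likely orders. An allocation is certain once one arm has used both its places.

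| Position | Probability that it is certain | Probability that the best guess is right |
|---|---|---|
| 1 | 0 | 1/2 |
| 2 | 0 | 2/3 |
| 3 | 1/3 (first two match) | 1/3 × 1 + 2/3 × 1/2 = 2/3 |
| 4 | 1 | 1 |
| Sum | 4/3 | 17/6 |

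- Per complete block: (4/3)/4 = 33.3% certain.
- 54 = 13 × 4 + 2, and the two patients in the last, incomplete block are never certain. Expected number: 13 × 4/3 = 17.3, and 17.3/54 = 32.1%.
- Range: at least 13 (the fourth place in every block), at most 26 (third and fourth in every block), or 24% to 48% of 54.

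**Best guess.** The rule is to guess the arm with more places left. Per complete block this is right (17/6)/4 = 70.8% of the time. Over 54 patients: 13 × 17/6 + 1/2 + 2/3 = 38.0, or 70.4%, against 50% with no information.

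**Effect of varying the block size.** Sequences of 54 were simulated for an investigator who knows the set of possible sizes but not which is in use, and who updates after every assignment.

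| Block sizes | Certain | Best guess right |
|---|---|---|
| 4 only | 32% | 70% |
| 2, 4, 6 at random | about 4% | 70% |
| 4, 6 at random | just under 6% | 69% |
| 4, 6, 8 at random | about 2.5% | 68% |

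Varying the size removes most of the certainty and little of the guessability. Adding blocks of two gains nothing on guessing, because a block of two is itself the easiest to guess: (1/2 + 1)/2 = 75%.

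**Balance.** If enrolment stops at 54, fixed fours give 28:26 when the first two places of the last block match, which has probability 1/3. The half-width is then 0.364 at most. With 4, 6 and 8 the worst split is 29:25, which was rare in the simulation, and the half-width is again 0.364 at most. Both round to the stated 0.36.

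**The case against.** The strongest reply is that deducing a slot is not the same as filling it with a chosen patient. Eligibility follows pre-defined criteria. Consent comes before randomization and may precede day 0 by up to 21 days. Patients are asked to stop NSAIDs at least one week before treatment. Many will therefore be consented and scheduled before their slot is known, and any allocation in between moves the slot. Recruitment does not rest on the waitlist alone. Knowledge of the block size and tracking of assignments are also inferred; the article does not state them.

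Much of this stands, and it narrows the opportunity. It does not close it. The order in which patients are approached, the order in which day-0 visits are booked, and a late decision not to proceed all stay with someone who could know the next assignment.

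A reader might infer that the design removes the main remaining protection against bias, or that no analysis could help. The documents do not support that. About two thirds of allocations are not certain. The outcome is a change from baseline, and the Data collection, management, and analysis section provides for adjustment for measured differences. What adjustment cannot reach is selection on unmeasured prognosis or expectation.

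A reader might also object that blocks of four cannot ensure 27:27 because 54 is not a multiple of four. That is arithmetically true, but immaterial to precision, and a condensed article need not describe how the last block is handled.

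**Conclusion.** The point holds as a weakness in concealment. An investigator who knows the block size and tracks assignments could deduce about one third of allocations with certainty: 4/3 per block, about 17 of 54. The count rests on two assumptions: that the printed block size is known to the person enrolling, and that past assignments are remembered. Both are reasonable in an open single-centre trial where the investigator takes the envelopes. It also rests on one unstratified sequence, since none other is described.

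The finding concerns opportunity. Nothing in the article shows that selection bias occurred or would occur, and it gives no basis for putting a figure on such bias. The 70% best-guess rate should not be presented as a harm that varied blocks would cure, because it hardly changes. The change is worth making because it is cheap and removes nearly all of the certainty.

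**What to change.** Before the first patient, or for the unassigned remainder if enrolment has begun:

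1. The statistician regenerates the list with block sizes chosen at random, such as 4, 6 and 8. Avoid blocks of two.
2. The protocol says only that block sizes vary. The sizes stay with the statistician and are withheld from the investigator, and from anything published, while enrolment is open.
3. Each assignment is released only after consent, study-knee choice and the day-0 WOMAC are recorded. Consent before randomization is already in the plan, and participants enter their answers before they see the examining physician. What needs stating is that these steps come before the envelope is opened. If possible, release from a list the investigator cannot see; the study's REDCap database is a natural place.
4. State that this lowers certain allocations from about 32% to about 2.5% (just under 6% with 4 and 6), while best-guess accuracy stays at 68% to 69%. The order of steps in item 3 therefore matters as much as the block sizes.

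The cost is a new list from the statistician and a small protocol modification submitted to the IRB. Release through REDCap would also need setting up and testing; keeping envelopes avoids that. The statistical downside is a worst split of 29:25 rather than 28:26 at 54 patients, with no visible loss of precision. The list should not be forced to end at exactly 27:27, since anyone who knows N could then deduce the last assignment.

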### Data collection, management, and analysis

Demographics and survey data will be stored using a REDcap database created specifically for the purpose of this study. REDcap has several security features, including off-site backups, an audit trail, secure logins, de-identified data exports, and built-in filtering methods to ensure data quality. Additionally, survey answers (clinical outcome data) will be directly entered into the database by the participants via iPad before they interact with the examining physician. Documentation not included in the quantitative analysis of clinical outcomes will be recorded using traditional source documents (Additional files 2 and 3). These documents will be kept in the participant’s binder and locked in a secure location. All data collection will take place in the clinic.

Only those who require access to the database will be given access. Coding of the variables will be done within the database. A completed data file will be stored by the statistician in the shared folder for the Clinical Translational Science Institute Biostatistics core at USC and will be backed up regularly. The statistician’s access to the database will be limited to de-identified data. Data quality will be assured by range checks for unusual or impossible data values. Data management will include a thorough data cleaning (checking ranges, evaluating distributions) and deriving of variables needed for analysis.

All protocol deviations will be recorded. The same outcome data will be obtained from all participants, regardless of protocol adherence. In order to promote retention and compliance, participants that receive the HA treatment and complete all schedule follow-up visits will be offered the fat treatment at the 6-month (final) follow-up visit at no charge. Imputation will be used if loss to follow-up is uncommon.

Preliminary analyses will include descriptive statistics of basic demographic and clinical characteristics to assess the degree to which randomization was effective in balancing treatment groups. If any factors are found to have clinically significant differences, they will be considered and evaluated as possible confounders. The analysis will be by intent-to-treat. That is, all subjects will be analyzed according to randomization status, regardless of actual treatment received, compliance with therapy, or adherence to the study protocol. We will compare the outcome, difference in WOMAC-A score from baseline to 6 months, between the treated and untreated groups using generalized linear models (GLM) with a Gaussian family specified, assuming the data are normally distributed. If the data are not normally distributed, we will specify a more appropriate distribution based on an evaluation of the data via histogram. We will also use GLM to examine the relationship between the treatment and outcome at each time point at which the WOMAC was measured. Last, we will model the effect across all time points using a multi-level mixed effects model to account for repeated measures. Confounders will be defined as those variables that were found to differ between groups either at baseline or post-randomization and which, when added to the model, alter the effect estimate by > 15%. Potential a priori confounders include BMI, Bilateral vs contralateral OA, gender, ethnicity, and race. Potential interactions between treatment and visit will be evaluated. A *p*-value of <.05 will be considered statistically significant. The 29-point PROMIS® questionnaire will be evaluated using GLM at each measured time point and across time points using a multi-level mixed effects model, as described above. Missing data, if ≤5%, will be imputed using multiple imputation methods. Any covariate missing > 5% will not be included in the analysis.

A per-protocol analysis will also be conducted including only those participants who were protocol-adherent. Protocol adherence is defined as: (1) Receiving the assigned study treatment and (2) completing all follow-up visits. Lastly, sensitivity analyses will be conducted to assess the impact of using multiple imputation methods, if such methods are employed in the analysis.

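### The primary WOMAC-A change-score model does not pre-specify baseline WOMAC-A as a covariate, so a trial whose main aim is precision gives up precision it could have from data already collected

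*Protocol article*

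**What the plan says.** Under Data collection, management, and analysis, the primary comparison reads: "We will compare the outcome, difference in WOMAC-A score from baseline to 6 months, between the treated and untreated groups". The model is a Gaussian GLM. No baseline WOMAC-A term is mentioned for this model, for the comparisons at each time point, or for the mixed model across visits.

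The same section governs covariates. The candidates named in advance are: "Potential a priori confounders include BMI, Bilateral vs contralateral OA, gender, ethnicity, and race". Baseline WOMAC-A is not among them. Other variables have a conditional route: "If any factors are found to have clinically significant differences, they will be considered and evaluated as possible confounders". A confounder is then a variable that differs between groups and "which, when added to the model, alter the effect estimate by > 15" per cent.

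On randomization, Assignment of interventions says: "Blocks of four were used to ensure equal numbers of subjects in each group". No stratification by baseline pain is described.

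The sample-size paragraph gives the purpose: "Since our primary aim is to estimate the effect size for future well-powered studies, we estimate the precision around which we can measure the effect". For that calculation, "we assumed standard deviations in the control and treatment groups of 0.66 and 0.67, respectively", and 27 patients per group give a 95% confidence interval of ±0.36. The Discussion says the sample size is fixed by funding. Table 1 schedules the WOMAC at screening, day 0, week 6 and month 6.

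**The concern.** A patient's own baseline pain score usually helps to predict the follow-up score. Subtracting it, as a change score does, amounts to fixing the regression slope of follow-up on baseline at 1. Estimating the slope (analysis of covariance, ANCOVA) is in large samples at least as precise, and more precise whenever the true slope differs from 1.

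The conditional confounder rule does not secure this gain. If the groups happen to be balanced at baseline, the rule leaves baseline WOMAC-A out and the precision is not recovered. If they are not balanced, the content of the primary model is decided after looking at the data.

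At stake is the width of the interval around the effect size that this trial exists to supply to later studies. With the sample size fixed, adjustment for a variable already collected is one of the few ways left to narrow it.

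**Working it through.** **Inputs from the protocol article.** 27 per group; SDs 0.66 and 0.67; two-sided 95% interval; HA mean change −0.84 with SD 0.67; −1.4 in the adipose group at 80% power.

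**Inputs that are assumptions.** The correlation r between baseline and 6-month WOMAC-A, and the ratio k of the 6-month SD to the baseline SD. The documents give neither. I use r = 0.3, 0.5 and 0.7, with k = 1 and k = 1.3, and take the planning SD as the SD of the unadjusted change.

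**1. Reproduce the plan's figures.** The standard error is √(0.66²/27 + 0.67²/27) = 0.181. The half-width is 1.96 × 0.181 = 0.355 (normal) or 2.007 × 0.181 = 0.363 (t, 52 df). Both round to the stated 0.36. The detectable difference at 80% power with SD 0.67 is 0.521 (noncentral t). That puts the adipose mean at −0.84 − 0.52 = −1.36, which is −1.4 to one decimal. Both figures fit an unadjusted change-score comparison.

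**2. Variance with and without adjustment.** With baseline SD s:

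- Var(change) = s²(1 + k² − 2rk)
- Var(ANCOVA residual) = s²k²(1 − r²)
- Ratio = k²(1 − r²)/(1 + k² − 2rk), which is (1 + r)/2 when k = 1

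The adjusted half-width is 2.008 (t, 51 df) × 0.181 × √ratio.

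| k | r | slope rk | variance ratio | half-width | detectable difference |
|---|---|---|---|---|---|
| unadjusted | – | – | 1 | 0.363 | 0.521 |
| 1 | 0.3 | 0.30 | 0.65 | 0.293 | 0.420 |
| 1 | 0.5 | 0.50 | 0.75 | 0.315 | 0.451 |
| 1 | 0.7 | 0.70 | 0.85 | 0.335 | 0.480 |
| 1.3 | 0.3 | 0.39 | 1.538/1.91 = 0.81 | 0.326 | 0.467 |
| 1.3 | 0.5 | 0.65 | 1.268/1.39 = 0.91 | 0.347 | 0.497 |
| 1.3 | 0.7 | 0.91 | 0.862/0.87 = 0.99 | 0.362 | 0.518 |

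With k = 1, the unadjusted analysis would need 54/0.65 = 83, 54/0.75 = 72 or 54/0.85 = 64 patients to match. With k = 1.3 the corresponding totals are about 67, 59 and 55.

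**3. Small-sample check.** A simulation with k = 1 and 54 patients (10,000 trials per value of r) gave variance ratios of 0.67, 0.78 and 0.87 against the theoretical 0.65, 0.75 and 0.85. The half-widths become 0.363 × √0.67 = 0.30, 0.363 × √0.78 = 0.32 and 0.363 × √0.87 = 0.34. Estimating the slope costs a little, and most of the gain remains.

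**4. Where chance imbalance sits.** Var(change) = Var(ANCOVA) + (1 − slope)² × Var(baseline imbalance). With k = 1, r = 0.5 and s = 0.67, per patient: 0.4489 = 0.3367 + 0.25 × 0.4489. The imbalance term, 0.1122, is 25% of the total, which is the whole difference between the two analyses. A one-standard-error imbalance, 0.67 × √(2/27) = 0.182, moves the change-score estimate by 0.5 × 0.182 = 0.091, and the ±0.36 already contains that movement.

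**5. How the 15% rule behaves.** At the planning difference of 1.4 − 0.84 = 0.56, 15% is 0.084. With the same assumptions, chance imbalance moves the estimate by more than this with probability P(|Z| > 0.084/0.091 = 0.92), about 0.36. On that criterion alone, baseline would enter in roughly a third of trials and stay out of the rest. The rule also requires an observed difference between groups, so the actual share could be lower.

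**The case against.** The plan is coherent as written: the outcome is a change, the precision is calculated for an unadjusted comparison, and the analysis compares changes. The published figures reproduce. This stands, and the point is about efficiency, not error.

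Four stronger readings are tempting, and the documents do not support them:

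- **Bias.** A reader might infer that regression to the mean biases the change score. Over repeated randomizations it does not. The estimate is off only conditionally on the imbalance observed.
- **Two harms.** A reader might count lost precision and exposure to baseline imbalance separately. Step 4 of the working shows that they are the same variance.
- **A guaranteed gain.** A reader might infer that adjustment helps whenever r is below 1. That holds for equal SDs. In general the gain depends on the slope and vanishes when the slope is 1. The article expects variability between the adipose preparations, so a larger SD at follow-up is plausible. Nor does it say whether the borrowed SD was raw or already baseline-adjusted.
- **Treatment as the only term.** The article does not say so. Its confounder list is open, and it is a condensed account with any analysis plan unseen.

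The last point carries some weight, but the article itself states the outcome form, the model family, the named candidates and the entry rule. Neither the open list nor the conditional rule secures baseline WOMAC-A in the primary model. The rule does deal with some imbalances, but only after the data have been inspected.

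**Conclusion.** The point holds as one of efficiency and pre-specification. The primary analysis is valid, and ±0.36 is correct for it. It leaves baseline WOMAC-A to a data-dependent rule, although precision is the primary aim and the variable is already collected.

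With r from 0.3 to 0.7, the half-width would fall from 0.36 to about 0.29 to 0.34 with equal SDs (8% to 19% narrower), or to about 0.33 to 0.36 if the 6-month SD is 1.3 times the baseline SD, with essentially no gain at r = 0.7. These ranges rest on assumed correlations and SD ratios, and on taking 0.66 and 0.67 as SDs of unadjusted change. The change is worth making, but the trial's validity does not depend on it.

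**What to change.** State that the primary model includes baseline WOMAC-A as a fixed covariate whatever the observed balance, outside the 15% rule. Do the same for each PROMIS-29 score when it is analysed as its own outcome. Keep the unadjusted change comparison as a sensitivity analysis.

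Define baseline explicitly. Table 1 places WOMAC at both screening and day 0, and places randomization on day 0 without giving the order. A reader might assume that the day-0 score precedes randomization, but the article does not establish this. Because the trial is unblinded, the covariate must come from an assessment completed before randomization, and the plan should say whether that is screening or day 0. PROMIS-29 is first scheduled on day 0, so its order relative to randomization needs stating too.

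The cost is one degree of freedom in each model and the wording above. No new data are needed if the chosen assessment is completed before randomization.
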